## Abstract

**Background:**

As patient care becomes more complex, high-quality communication and relationships among healthcare professionals are critical to coordinating care. Relational coordination (RC), a process of high-quality communication supported by shared goals, shared knowledge, and mutual respect, is positively associated with better patient (e.g., quality of care) and staff (e.g., job satisfaction, and retention) outcomes. A few researchers have found that communication skills training improves RC in civilian hospitals. However, researchers have not tested the feasibility of conducting communication skills training based on the RC framework among healthcare professionals in military hospitals. To address this gap, we propose conducting an RC training intervention in a military hospital. The primary aim of the proposed pilot study is to determine the feasibility (e.g., recruitment, retention, and completion rates) of conducting an RC training intervention in an Army medical center. The secondary aim is to explore the acceptability and usability of the RC training intervention. We will also explore changes in RC, quality of care, job satisfaction, and intent to stay among participants following the RC training intervention.

**Methods:**

A single-group feasibility study will be conducted among nurses and physicians from three units (intensive care unit, medical-surgical, and labor and delivery unit). A convenience sample of licensed practical nurses (LPNs), registered nurses (RNs), resident physicians, and physicians from the participating units will be invited to complete a 1-h RC training intervention once a month for 3 months. Participants will complete RC, quality of care, job satisfaction, and intent to stay measures at baseline and 2 weeks after each RC training intervention session. To assess the feasibility of conducting an RC training intervention, we will examine recruitment/retention rates, intervention session completion rates, and survey measure completion rates. Acceptability will be assessed qualitatively through focus group interviews, and results will be used to refine the intervention and determine if the selected measures align with participant experiences. For our secondary aim, we will explore the acceptability of the RC training intervention through focus group interviews. We will also explore changes in outcome measures using descriptive statistics with 95% confidence intervals.

**Discussion:**

Findings will establish the feasibility and acceptability of conducting an RC intervention in a military hospital and inform refinement of the intervention and study procedures prior to conducting a larger randomized controlled trial to establish efficacy.

**Supplementary Information:**

The online version contains supplementary material available at 10.1186/s40814-025-01596-7.

## Background

Patient care is becoming more complex, as patients are presenting with uncertain diagnoses and multiple co-morbidities [1, 2]. This is a critical problem within the healthcare system as healthcare professionals are challenged to meet the increased time constraints and demands that accompany caring for complex patients. As patient care becomes more complex, high-quality communication and relationships among healthcare professionals are critical to coordinating care [3–6]. While uncoordinated care is a problem in civilian healthcare settings, military healthcare settings may encounter additional barriers to coordinating care because of the unique hierarchical ranking structures that exist among healthcare professionals in military hospitals [7, 8]. Understanding RC in a military context poses a unique opportunity to examine a complex organizational structure due to the presence of clear authority gradients and differences in military rank. Additionally, explicit, formal power differences exist between enlisted service members, commissioned officers, and members in different ranks within each personnel structure. These hierarchical ranking structures create power differences among healthcare professionals in different ranks. Power differences among members in a workgroup can negatively influence communication and relationships [9], leading to lower job satisfaction and retention.

Relational coordination (RC), defined as “a mutually reinforcing process of communicating and relating for the purpose of task integration within and between roles,” ([10] p. 301) is a unique way to coordinate care among healthcare professionals involved in complex work processes. RC encompasses four communication dimensions (frequent, timely, accurate, and problem-solving communication) and three relationship dimensions (shared goals, shared knowledge, and mutual respect) [10, 11] See Table 1.

**Table 1 Tab1:** Dimensions and definitions of relational coordination [10, 11]

Seven relational coordination dimensions	Definitions
Frequent communication	How often professionals communicate regarding their work process
Timely communication	How soon professionals report significant information regarding a work process
Accurate communication	Preciseness of information communicated between professionals regarding a work process
Problem-solving communication	The extent to which professionals seek solutions instead of placing blame when problems occur
Shared goals	Understanding how the work of each professional fits together with the work of other professionals in the same work process
Shared knowledge	An understanding of the role of other professionals, which includes an awareness of who needs to know what and why and when
Mutual respect	Valuing the work of other professionals

Researchers have sought to address the problem of coordinating patient care for complex patients through RC and communication skills training [12–15]. In observational studies, RC has been associated with improved patient outcomes (e.g., quality of care) [16] and better staff outcomes (e.g., higher job satisfaction and retention) among nurses and physicians in civilian hospitals [13, 17–20]. A few researchers have also conducted communication skills training to improve RC among civilian healthcare professionals, and in these studies, patient outcomes improved [14, 15]. Fettig et al. [14] found that communication skills training improved RC about goals of care among nurses, physicians, social workers, and chaplains in an intensive care unit. Blakeney et al. [15] conducted a 4-year longitudinal study consisting of various training interventions (leadership workshops, interprofessional team training, and structured bedside rounds) to improve RC among healthcare professionals in a heart failure unit. Blakeney et al. [15] found that these interventions significantly improved RC scores (*p* = 0.0001) from baseline to year 4.

Although these studies show significant positive results regarding communication skills training to improve RC [14, 15], additional research is needed to determine the feasibility and acceptability of conducting RC training interventions. Moreover, the current literature is limited to civilian healthcare settings. Given that communication skills training improved RC in civilian hospitals [14, 15], we believe communication skills training will improve RC and other outcomes—such as quality of care, job satisfaction, and intent to stay—in unique settings such as military hospitals. Thus, we propose conducting communication skills training based on the RC framework in a military hospital. The primary aim of the proposed pilot study is to determine the feasibility (e.g., recruitment, retention, RC training completion rates, and survey completion rates) of conducting an RC training intervention in an Army medical center. The secondary aim is to explore the acceptability and usability of conducting an RC training intervention. We will also explore group-level changes in RC and individual-level changes in quality of care, job satisfaction, and intent to stay among nurses and physicians following an RC training intervention. We will explore the following research questions: (1) what percent of eligible participants consent to participate in the study? (2) What percent of intervention sessions do participants complete? (3) What percent of survey measures do participants complete? and (4) What are the nurses’ and physicians’ perspectives about the acceptability and usability of the RC training intervention for improving their relationships and communication on their unit, quality of care, job satisfaction, and intent to stay? Given the significant results between RC and patient and staff outcomes in prior studies, we expect that an RC training intervention will improve the quality of care, job satisfaction, and intent to stay in our study.

## Methods

### Design, setting, and ethics

This single-group feasibility study will be an extension of a previous study exploring RC, job satisfaction, and intent to stay [21]. We conducted a secondary analysis and found that participants from the intensive care, medical-surgical, and labor and delivery unit in an Army medical center reported lower job satisfaction and intent to stay. Thus, we will invite healthcare professionals from these units to participate in an RC training intervention. Our reporting follows the SPIRIT guidelines (see SPIRIT checklist in supplemental files). The Indiana University Institutional Review Board approved this study (Approval number 15936). Any significant protocol modifications will be communicated to participants and the institutional review board prior to implementing any changes.

### Sampling and recruitment

This is a feasibility study and is not a priori designed to detect clinically meaningful changes in this pilot stage. Three units will be invited to participate in this study. All units are expected to participate, with approximately twelve participants from each unit enrolling (*n* = 36) and six participants from each unit completing (*n* = 18, 50%). With a sample size of 36 enrolling, a two-sided 95% exact (Clopper-Pearson) confidence interval would have a margin of error of 17% when the completion rate is 50% [22]. Potential participants will be identified using the protocol inclusion and exclusion criteria. The principal investigator will conduct virtual meetings with nurse managers, physician leaders, and eligible participants and provide a detailed overview of the study. The principal investigator will also email a detailed overview of the study, the voluntary nature of participation, the consent process, and the assurance that participant responses will remain confidential to eligible participants. The research team will place flyers on participating units and send a follow-up email to eligible participants to inform them about the study and how to contact the research team if they desire to participate. The primary investigator will obtain verbal consent from participants prior to beginning the study (e.g., surveys, RC training intervention, focus group interviews). A five-dollar coffee card will be offered at each data collection time point to incentivize participants to complete the surveys at each data collection time point.

### Inclusion and exclusion criteria

Participants who meet the following inclusion criteria will be invited to participate in the study: (1) licensed practical nurses; (2) registered nurses; (3) physician residents; (4) physicians; (5) able to read and understand the English language; (6) employed at least 3 months at the study site; and (7) speaks and understands the English language. While the participants must be able to speak and understand the English language, our training will be inclusive and sensitive to diversity (e.g., we will include participants who speak English as a second or additional language). Exclusion criteria will be healthcare professionals who are government contractors (temporary employees).

### The RC training intervention

The RC training intervention will be conducted face-to-face after participants complete the baseline survey and RC knowledge assessment. See Additional files 1 and 2. The RC training intervention will be delivered by a member of the relational coordination collaborative group. The relational coordination collaborative group is a community of professionals from various sectors around the world who use RC in their research and practice. A 1-h RC training session will be delivered each month for 3 months, for a total of three sessions. Session one will explore the RC dimensions and evidence-based literature supporting RC and patient and staff outcomes [20, 23, 24]. Session two will be conducted 1 month later and focus on a relational mapping exercise. Relational mapping allows participants to generate new ideas for how they communicate and relate to each other regarding complex work processes [25]. Session three will be conducted 1 month after session two and will explore how to operationalize RC on their unit [26]. During the third RC training session, we will help participants identify effective strategies to improve interprofessional collaboration, quality of care, job satisfaction, and intent to stay using the dimensions of RC. See Table 2. Participants will be advised that may leave the RC intervention training sessions for any reason and at any time if they.

**Table 2 Tab2:** RC training intervention overview

Relational coordination training session 1 (1 h lunch and learn)	
Objectives	• Discuss the relational coordination dimensions and organizational change model • Review relational coordination and patient and staff outcome studies
Relational coordination training session 2 (1 h lunch and learn)	
Objectives	• Participants will create color-coded relational ties between healthcare professionals involved with patient care on their unit • Identify which healthcare professionals have weak relational ties • Identify which healthcare professionals have strong relational ties • Discuss why these weak and strong relational ties exist and ways to improve weak relational ties among healthcare professionals
Relational coordination training session 3 (1 h lunch and learn)	
Objective	• Discuss how to operationalize the relational coordination dimensions • Discuss how relational coordination can be used in conjunction with TeamSTEPPS to improve patient and staff outcomes

^*^Team STEPPS (Team Strategies and Tools to Enhance Performance and Patient Safety)

### Fidelity assessment

The RC training intervention will be delivered using a standardized manual and session-specific checklists to ensure consistent delivery across facilitators and groups [27, 28]. A member of the relational coordination collaborative group will deliver the training intervention. Prior to delivering the sessions, the relational coordination collaborative group member will attend 2 h of training consisting of didactics and role-playing. Each session will be audio recorded and reviewed by two members of the research team using fidelity checklists (e.g., to determine if the training intervention was delivered as intended and consistent with the protocol). Two members of the research team will use a checklist of intervention content to independently code recordings.

### Study procedures

Data collection will occur at baseline and 2 weeks after the completion of each RC training intervention session. The surveys (RC, RC knowledge assessment, quality of care, job satisfaction, and intent to stay) will be distributed at the following time points.

Baseline (prior to the RC training intervention).

Two weeks after the RC training intervention Session 1.

Two weeks after RC training intervention Session 2.

Two weeks after the RC training intervention Session 3.

Participants will complete the survey electronically by scanning a QR code. We selected these data collection time points to explore patterns across workgroups (e.g., nurses and physicians) over time and refine subsequent RC training sessions based on survey results at each data collection time point. For example, if participants report low frequent communication scores, we can explore why participants rated this RC dimension less favorably and discuss ways to improve frequent communication during the subsequent RC training session. RC training intervention evaluations will be used to explore the acceptability of the training sessions, and we will administer the evaluation via Survey Monkey immediately after each RC training intervention session. Two weeks after the final RC training is complete, participants will be invited to participate in a 30–45-min focus group interview session, during which we will explore the acceptability of the intervention. See Table 3 for the study procedures timeline.

**Table 3 Tab3:** Study procedures timeline

Activity	Quarter 3 2022	Quarter 1 2023	Quarter 2 2023	Quarter 3 2023	Quarter 4 2023	Quarter 1 2024
Prepare recruitment materials	X					
Meeting with Chief Nursing Officer and Chief Medical Officer at the study site	X					
Submit IRB Application	X					
Set up database and meeting with nurse and physician leaders of the participating units		X				
Distribute recruitment materials/letters to eligible participants			X			
Distribute baseline survey and RC knowledge assessment				X		
RC training intervention session 1				X		
RC training intervention session 2				X		
RC training intervention session 3				X		
Focus group interview session				X		
Data cleaning and entry				X	X	
Data analysis				X	X	
Dissemination of results						X

^*^Relational coordination (RC)

### Primary outcomes

We will use a mixed methods approach to establish feasibility. As such, we will collect data on feasibility as outlined below.

#### Feasibility

We will collect data on feasibility by assessing the following: (1) recruitment and retention rates; (2) the percent of eligible participants who consent to participate in the study; (3) the percent of planned intervention sessions participants complete; (4) the percent of planned measures participants complete (e.g., the number of participants who complete the survey at baseline and 2-weeks post each RC training intervention session). We will also collect data on the number of participants who participated in all three RC training intervention sessions. See Table 4 for the feasibility benchmark outcomes.

**Table 4 Tab4:** Feasibility benchmark outcomes

Feasibility outcome	Feasibility benchmark of success
Recruitment rates	We will recruit at least 12 participants per unit
Retention rates	We will retain at least 50% of participants per unit (*n* = 6)
Percent of eligible participants who participate in the study	At least 50% of eligible participants per unit will consent to participate
Number of intervention sessions participants complete	Participants will complete at least two RC training intervention sessions
Percent of participants who complete the surveys at each data collection time point	At least 50% of eligible participants will complete the surveys at each data collection time point
Number of participants who participate in each RC training intervention session	At least six participants per unit will participate in each RC training intervention

*RC* relational coordination

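### Table 4 sets the survey-completion benchmark on eligible staff, although the outcome counts participants; the planned case reads as 25% or 50% depending on the denominator

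*Protocol article*

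**What the plan says.** The relevant statements in the protocol article are these.

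- Feasibility, Table 4, survey row: the label is "Percent of participants who complete the surveys at each data collection time point" and the benchmark is "At least 50% of eligible participants will complete the surveys at each data collection time point".
- Table 4, consent row, two rows above: "At least 50% of eligible participants per unit will consent to participate".
- Table 4, retention row: "We will retain at least 50% of participants per unit", with six given as the number.
- Table 4, recruitment row: "We will recruit at least 12 participants per unit".
- Feasibility, outcome (4) in the text, and research question 3 in the Background: both express survey completion as a percentage of measures that participants complete.
- Sampling and recruitment: "approximately twelve participants from each unit enrolling" (36 in all) and "six participants from each unit completing" (18 in all, 50%). Verbal consent is obtained before any survey.
- Study procedures: surveys fall at baseline and two weeks after each of three sessions, so there are four time points.

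**The concern.** The consent row, research question 1, the recruitment text and the timeline in Table 3 all use eligible participants for people who have not yet consented. If the term means the same in the survey row, that row divides by a pool that includes staff who decline and so are never surveyed. The threshold then conflicts with its own row label and with outcome (4). It also sits badly beside the consent and retention rows, because a study that only just meets both has little or no room to meet this one.

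Feasibility is the primary aim, and this is one of six benchmarks stated in advance. If the denominator is unclear, the same returns can be reported as success or failure, and the choice could be made after the data are known.

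**Working it through.** **Inputs.** From Sampling and recruitment: 12 enrolled and 6 completing per unit, three units, 36 and 18 in all. From Table 4: consent of at least 50% of eligible staff, retention of at least 50% of participants, survey completion of at least 50% at each time point. The article does not give the number of eligible staff. If the recruitment and consent benchmarks are both met exactly, it is 12 / 0.50 = 24 per unit, or 72 in all. This is an implied figure, and a range is shown in step 5.

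**1. The plan's own figure.** For 18 of 36, the exact two-sided 95% interval is 32.9% to 67.1%, a half-width of 17.1%. The stated 17% margin reproduces. It is computed on the 36 enrolled, so the issue below does not affect it.

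**2. Upper limit at 50% consent.** Completion among eligible staff = consent rate x response rate among those who consent. With 50% consent and every enrollee responding, this is 0.50 x 1.00 = 50% (12/24). That meets the benchmark exactly and leaves no room for a single missed survey. This limit holds at all four time points, baseline included, and needs no assumption about retention.

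**3. Planned case at the last time point.** Assume that a person who is not retained does not return the last survey.

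- Eligible staff as denominator: 0.50 x 0.50 = 25%, which is 6/24 per unit or 18/72 overall. The benchmark is missed.
- Enrolled participants as denominator: 6/12 = 50% per unit, or 18/36 overall. The benchmark is just met.

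**4. When the row can be met as written.** Under the same assumption, consent x retention must be at least 50%. At 50% consent, retention must be 100%; at 50% retention, consent must be 100%. About 71% on each also suffices, since 0.71 x 0.71 = 0.504.

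**5. Sensitivity to the size of the pool**, with 12 enrolled and 6 returning the last survey:

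| Eligible per unit (assumed) | Consent | Completion among eligible |
|---|---|---|
| 12 | 100% | 50% |
| 15 | 80% | 40% |
| 18 | 67% | 33% |
| 20 | 60% | 30% |
| 24 | 50% | 25% |

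Every pool in the table satisfies the consent benchmark. Only the smallest satisfies the survey benchmark as written.

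**The case against.** The best defence is that the intended denominator can be read from the article. The row label, outcome (4) and research question 3 all speak of participants, and the precision statement uses the 36 enrolled. One table cell adds the word eligible, which is probably a slip rather than a design error. This stands, and it limits how serious the point is. It does not remove the point, because the cell with the stray word is the one that states the success threshold.

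A reader might infer that the survey benchmark must fail. The documents do not support that. All the benchmarks are minimums, and higher consent and retention would pass. The 25% figure also depends on a link that the article does not define: neither retention nor completing is stated to mean returning the last survey. Surveys are answered electronically by QR code, so someone who misses sessions could still respond. If every consenter did so at 50% consent, the result would be exactly 50%, which passes.

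A reader might also infer that missing this row would make the study infeasible. The article gives no such rule. It says that feasibility outcomes will be summarised descriptively and will inform refinement of the intervention and procedures. With enrolled and completing counts in hand, the rate could be reported on either denominator, provided the number of eligible staff is also recorded.

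**Conclusion.** The point holds as an inconsistent denominator in a success criterion fixed in advance. As written, the survey row conflicts with its own label and with outcome (4). At the 50% consent benchmark it can be met only if every enrollee answers at every time point; this part rests only on consent preceding the surveys.

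The larger contrast, 25% of eligible against 50% of enrolled in the planned case, rests on two assumptions: that consent is exactly at its benchmark (24 eligible per unit), and that people who are not retained do not return the last survey. The second is plausible, since Sampling and recruitment describes the six per unit as completing, but it is not stated.

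The consequence is limited to this benchmark: it would be reported as missed when the study went as planned, or its denominator would be settled after the results are known. The sample size, the 17% margin and the other five benchmarks are unaffected. It should be corrected, but as a clarification of wording rather than a fault in the design.

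**What to change.** In the survey row of Table 4, replace the word eligible with enrolled (consented), leaving the 50% threshold and the four time points as they are. Keep eligible as the denominator in the consent row only. If eligible staff really is the intended denominator for surveys, say so, change the row label and outcome (4) to match, and reset the threshold so that it is consistent with the consent and retention rows.

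The cost is one word in one table row and a short protocol amendment, with no added participants, data or analysis. The change should be dated before survey completion is summarised, or, if that has already happened, reported with both denominators.
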